### 14.1.2 Serious adverse events

A serious adverse event is defined by regulatory agencies as one that suggests a significant hazard or side effect, regardless of the investigator’s or sponsor’s opinion on its relationship to investigational product. This includes, but may not be limited to, any event that (at any dose):

- is fatal
- is life-threatening (places the subject at immediate risk of death)
- requires in-patient hospitalization or prolongation of existing hospitalization
- is a persistent or significant disability/incapacity
- results in a congenital anomaly or birth defect

A hospitalization meeting the regulatory requirement for “serious” criteria is any in-patient hospital admission or prolongation hereof should be considered a serious adverse event.

Any event that does not exactly meet this definition yet which, in the investigator’s opinion, represents a significant hazard can be assigned the “other significant hazard” regulatory reporting serious criteria.

Additionally, important medical events that may not be immediately life threatening or result in death or hospitalization, but which may jeopardize a subject or require intervention to prevent one of the outcomes listed above, or result in urgent investigation, may be considered serious. Examples include allergic bronchospasm, convulsions, and blood dyscrasias.

Severity of adverse events

For each AE, severity will be graded accordingly:

- Mild: Transient symptoms, no interference with patient’s daily activities.
- Moderate: Marked symptoms, moderate interference with patient’s daily activities.
- Severe: Considerable interference with patient’s daily activities.

Relationship of AE to trial intervention

For each AE, relationship to trial intervention will be rated accordingly:

- Probable: Good reason and enough documentation to assume a causal relationship.
- Possible: A causal relationship is likely and cannot be excluded.
- Unlikely: The event is most likely related to an etiology other than the intervention.
- Unknown: Causality is not assessable.

An AE with a possible or probable relationship to the trial intervention will be categorized as an adverse reaction (AR).

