## 13.5 Reporting

At each assessment of an AE/AR, it must be evaluated if it should be categorized as a serious adverse event/ (SAE), and if so, this must be reported to the trial sponsor. The trial sponsor will evaluate all SAE/SAR.

Death resulting from circulatory collapse will be recorded but will not be reported to the ethical committee outside the annual reports, as AHF patients have a ≥20% risk of death within 30 days. The death rate will have no essential information in the monitoring of trial by authorities.

All SAEs occurring at the trial centers will be submitted once a year by the sponsor and a safety report of all trial patients will be submitted to the ethical committee.

No later than 90 days after the trial has been completed, the trial sponsor will notify the ethical committee, and if the trial is stopped earlier than planned, the reasons will be reported.

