## 13.6 Reporting Procedures for All Adverse Events

All adverse events occurring after inclusion observed by the investigator or reported by the subject (whether attributed to investigational product), will be reported on the case report form. Medically significant adverse events considered related to the investigational product by the investigator or the sponsor will be followed until resolved or considered stable.

The following attributes must be assigned by the investigator: description; dates of onset and resolution; severity; assessment of relatedness to investigational product, other suspect drug, or device, and action taken. The investigator may be asked to provide follow-up information.

It will be left to an investigator’s clinical judgment as to whether an adverse event is of sufficient severity to require a subject’s removal from treatment. A subject may also withdraw voluntarily from treatment because of what he or she perceives as an intolerable adverse event. If either of these situations arises, the subject must undergo an end-of-study assessment and be given appropriate care under medical supervision until symptoms cease or the condition becomes stable. If the subject was permanently withdrawn from the study or investigational product due to a serious adverse event, this information must be included in either the initial or follow-up Serious Adverse Event Report Form or the End of Study Case Report Form. Data on deaths and hospitalizations will be collected until study termination.

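### The causality scale defines Possible as a likely link, so a plausible but not likely link has no rating that counts as an adverse reaction

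*Protocol*

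**What the plan says.** Protocol Section 14.1.2, under the sub-heading on the relationship of AEs to the trial intervention, gives four levels:

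- The top level, *Probable*, asks for good grounds and adequate documentation that the intervention was the cause.
- The second level is worded as follows: "Possible: A causal relationship is likely and cannot be excluded".
- The third level turns on whether a different cause is the best explanation: "Unlikely: The event is most likely related to an etiology other than the intervention".
- The last level, *Unknown*, is kept for events that nobody can judge.

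The section then turns the rating into a class: "An AE with a possible or probable relationship to the trial intervention will be categorized as an adverse reaction (AR"). *Unlikely* and *Unknown* do not make an AR.

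Relatedness appears again in Section 13.6: "Medically significant adverse events considered related to the investigational product by the investigator or the sponsor will be followed until resolved or considered stable". Section 13.5 uses the AR label when it has the sponsor evaluate serious events and serious reactions.

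**The concern.** A scale of this kind needs a level for the event that the intervention might have caused but that something else might equally well explain. The label *Possible* suggests that level. Its definition does not provide it, because it also asks that the link be likely. Once a link is likely, saying that it cannot be ruled out adds nothing, and little then separates *Possible* from *Probable*.

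The gap matters more in this population than in most. The patients have acute heart failure, which is itself a competing explanation for much of what Section 14.1.1 collects (symptomatic hypotension, arrhythmia, renal replacement, intubation). Section 14 itself says that relating events to an intervention is difficult or impossible in these patients. Plausible but not likely is therefore a judgement that raters can expect to reach. At stake are the meaning and consistency of the AR/SAR label, and perhaps which events are followed until they settle.

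**Working it through.** The protocol states no figure on this point, so the check is one of logic. The inputs are the four definitions and the AR rule in Section 14.1.2. I take *likely* in its ordinary sense of more probable than not.

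| Judged link to the intervention | *Probable* | *Possible* | *Unlikely* | *Unknown* | AR? |
|---|---|---|---|---|---|
| Likely, good reason and documentation | met | also met | not met | not met | yes |
| Likely, documentation insufficient | not met | met | not met | not met | yes |
| Plausible, evenly balanced with another cause | not met | not met (not likely) | not met (no other cause is most likely) | not met (it was assessed) | no |
| Plausible, another cause more likely | not met | not met (not likely) | met | not met | no |
| Improbable | not met | not met | met | not met | no |

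Three results follow.

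1. Row 4 is scored with row 5. A link that cannot be ruled out receives the same rating as an improbable one.
2. Row 3 has no category. The scale is not exhaustive. A rater may fall back on *Unknown*, but neither that nor *Unlikely* makes an AR.
3. A rater guided by the label rather than the definition would put rows 3 and 4 under *Possible* and call them ARs. Two careful raters can therefore class the same event differently.

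I then looked for text elsewhere in the adverse-event sections that redefines *Possible* or rescues rows 3 and 4. There is none. Those sections in fact use a weaker sense. Section 14 speaks of events potentially related to the interventions, and Section 14.1.1 collects unlisted events on the same basis. An unlisted event can thus enter the AE record because it is potentially related and then fail the definition of *Possible*.

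How many events are affected cannot be computed. The protocol gives neither AE or AR rates nor any distribution of causality judgements.

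**The case against.** The strongest reply is that little safety information depends on this rating, and most of that reply stands.

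- Section 13.6 puts AEs on the case report form whether or not they are attributed to the intervention.
- Section 14.1.1 collects the listed events for 30 days without a causality condition.
- Section 14.1.2 defines seriousness independently of anyone's opinion on relatedness.
- Section 13.5 states: "All SAEs occurring at the trial centers will be submitted once a year by the sponsor". It sets no relatedness condition.
- The follow-up rule in Section 13.6 cites neither the four-level scale nor the AR label, and it lets the sponsor judge independently. Loss of follow-up is therefore a possibility and is not established.
- ARs are not an outcome in Section 7, and Section 12 plans no comparison of them. Section 14 says that benefit and harm will be judged through the primary and secondary outcomes.

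It can also be said that the label, and the phrase about not being able to exclude a link, both invite the everyday reading, so that many raters would do the sensible thing. That is fair, but it replaces uniform loss with inconsistent rating. It does not make the definition correct.

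A reader might go further and infer that most plausible reactions will be lost. The documents do not support a size. Suppose judged probabilities of causation are spread evenly from a to b, and *likely* starts at c. The share of events not counted is (c − a)/(b − a). All three inputs are assumptions:

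- 5% to 60%, cut-off 50%: 45/55 = 82%
- 5% to 95%, cut-off 50%: 45/90 = 50%
- 5% to 60%, cut-off 30%: 25/55 = 45%
- 30% to 90%, cut-off 50%: 20/60 = 33%

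The result moves from 33% to 82% on invented inputs alone, so none of these figures is an estimate for this trial.

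**Conclusion.** The definition of *Possible* is stricter than its label and leaves a gap in the scale. Read literally, an assessable event with a plausible but not likely link is *Unlikely*, or unclassifiable if evenly balanced, and is not an AR or SAR. Read by the everyday meaning of the label, it is one. The classification is therefore too narrow or inconsistent. This rests only on the wording of Section 14.1.2 and the ordinary meaning of *likely*.

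The effect is confined to the AR/SAR classification and possibly the follow-up of related events. AE recording, the yearly submission of serious events, the efficacy outcomes, the sample size and the significance level are untouched. The point is minor.

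Two further inferences should be resisted. A reader might conclude that the comparison of harm between the arms is biased. No AR comparison by arm is planned, and the intervention is to be given double-blind (Section 5.1), so nothing in the documents shows a mechanism that favours one arm. A reader might also cite the absence of a data safety monitoring board (Section 1.5) as an aggravating factor. Nothing in the protocol suggests that such a board would re-score causality, so that does not follow.

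**What to change.** Reword the middle level along these lines: *Possible: a causal relationship is conceivable and cannot be excluded, although another aetiology is also plausible.* The closing clause is a concession and not a further condition.

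Reserve *Unlikely* for links judged improbable. Its present test, that another cause is the most likely one, would overlap with the new *Possible*, so it needs a matching adjustment. State that the levels are applied from the top down and that the first one met is the rating. The scale is then exclusive and exhaustive, with *Unknown* kept for events that cannot be assessed. Leave the AR rule unchanged.

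It would also help to say in Section 13.6 whether an event considered related means one rated *Possible* or *Probable*.

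The cost is a few words in the protocol and the help text on the case report form. The downside is a somewhat higher AR count.

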## 13.5 Reporting

At each assessment of an AE/AR, it must be evaluated if it should be categorized as a serious adverse event/ (SAE), and if so, this must be reported to the trial sponsor. The trial sponsor will evaluate all SAE/SAR.

Death resulting from circulatory collapse will be recorded but will not be reported to the ethical committee outside the annual reports, as AHF patients have a ≥20% risk of death within 30 days. The death rate will have no essential information in the monitoring of trial by authorities.

All SAEs occurring at the trial centers will be submitted once a year by the sponsor and a safety report of all trial patients will be submitted to the ethical committee.

No later than 90 days after the trial has been completed, the trial sponsor will notify the ethical committee, and if the trial is stopped earlier than planned, the reasons will be reported.

## 13.6 Reporting Procedures for All Adverse Events

All adverse events occurring after inclusion observed by the investigator or reported by the subject (whether attributed to investigational product), will be reported on the case report form. Medically significant adverse events considered related to the investigational product by the investigator or the sponsor will be followed until resolved or considered stable.

The following attributes must be assigned by the investigator: description; dates of onset and resolution; severity; assessment of relatedness to investigational product, other suspect drug, or device, and action taken. The investigator may be asked to provide follow-up information.

It will be left to an investigator’s clinical judgment as to whether an adverse event is of sufficient severity to require a subject’s removal from treatment. A subject may also withdraw voluntarily from treatment because of what he or she perceives as an intolerable adverse event. If either of these situations arises, the subject must undergo an end-of-study assessment and be given appropriate care under medical supervision until symptoms cease or the condition becomes stable. If the subject was permanently withdrawn from the study or investigational product due to a serious adverse event, this information must be included in either the initial or follow-up Serious Adverse Event Report Form or the End of Study Case Report Form. Data on deaths and hospitalizations will be collected until study termination.

# 14. Timeline and enrollment

We expect to start inclusion per 1. May 2023

|  | **Pre-trial** | **Year 1** | | | | **Year 2** | | | | **Year 3** | | | |
| --- | --- | --- | --- | --- | --- | --- | --- | --- | --- | --- | --- | --- | --- |
| **Funding** |  |  |  |  |  |  |  |  |  |  |  |  |  |
| **Protocol development and modifications** |  |  |  |  |  |  |  |  |  |  |  |  |  |
| **Ethical approval** |  |  |  |  |  |  |  |  |  |  |  |  |  |
| **Creation of database** |  |  |  |  |  |  |  |  |  |  |  |  |  |
| **Trial registration** |  |  |  |  |  |  |  |  |  |  |  |  |  |
| **Creation of randomization list** |  |  |  |  |  |  |  |  |  |  |  |  |  |
| **Education of site personnel** |  |  |  |  |  |  |  |  |  |  |  |  |  |
| **Enrollment and assessment of outcomes** |  |  |  |  |  |  |  |  |  |  |  |  |  |
| **Writing and publication of Design article** |  |  |  |  |  |  |  |  |  |  |  |  |  |
| **Cleaning and closing of the database** |  |  |  |  |  |  |  |  |  |  |  |  |  |
| **Data analyses** |  |  |  |  |  |  |  |  |  |  |  |  |  |
| **Main manuscript-writing** |  |  |  |  |  |  |  |  |  |  |  |  |  |
| **Unblinding** |  |  |  |  |  |  |  |  |  |  |  |  |  |
| **Publication and presentation of results** |  |  |  |  |  |  |  |  |  |  |  |  |  |

# 15. Funding

The steering group has initiated the study. The trial will be funded by external foundations for medical research. The trial is an investigator-initiated trial, and the budget will be covering expected expenses only. Gangstedfonden has supported the project with 450.000 kr. When additional funding is received the ethics committee will be noticed.

# 16. Publication plan

All trial analyses will be conducted by the steering committee, and the results will be interpreted with treatment allocation coded as “1” and “2”. After acceptance of the analysis and conclusions by the steering committee, the trial will be unblinded.

## 16.1 Design paper

A design paper describing the study design, trial population definition including inclusion and exclusions criteria, endpoints as well as the planned statistical analyses plan will be submitted for peer review and publication well before the main trial data analyses will begin.

Authors of the Design paper will be IA (first author), Site Investigators, study statistician and steering group member. Additional authors may be included if the Steering Group allow it and provided, and they fulfil the Vancouver criteria.

## 16.2 Main results paper

Authorship will be granted according to ICMJE guidelines. The final manuscripts of the interventions will be submitted as 1 manuscript to a peer-reviewed international journal and the findings of the study will be published regardless the results suggesting a beneficial effect, neutral effect, or harm of the interventions. The main trial paper manuscript will be drafted according to the statistical analysis plan by the Steering group members. Authors of the main trial manuscript are all, who have contributed to the trail sufficiently to be a coauthor. The expected number of coauthors will be 5 members per site and additionally 1 person per 100 included patients, in addition to the following:

IA (first author), Steering group members, study statistician, primary investigator. The target journal is a high-ranking international medical journal.

The main trial results will be published regardless of being positive, neutral, or negative. The main trials will also be submitted for presentation at national and international conferences

## 16.3 Auxiliary manuscripts / post-hoc analyses

The steering group will manage post-hoc sub-study analysis and requests for sub-study proposals before the start of main trial data analysis. The purpose of the sub-study group is to ensure an even access to the sub-studies among the participating sites and others, to avoid overlap in published sub-studies and to oversee that sub-studies are progressing according to the plan.

# 17. Data sharing

The database will be maintained for 15 years and anonymized if requested by relevant authorities. There are currently no plans of data sharing. Research biobank data, secondary analyses of imaging materials or the main trial database for sub-studies will not be made publicly available.

# 18. Tasks and responsibilities

## 18.1 Sponsor/PI

Principle Investigator (JG): Sponsor, Coordination of protocol development, funding, ethical approval, information to sites, recruitment of trial sites, daily management, authorize invoices.

Senior Investigator (JH): Funding, information, recruitment of trial sites.

## 18.2 Steering group

Protocol development, funding, information to study participant and clinical personnel, recruitment of trial sites, sub-study coordination.

Additional sites

In case target enrolments are not met after 6 months of enrolment, additional regions of Denmark will be approached regarding participation in the trial.

# Appendix 2: Generic flow chart containing information on when and how to include patients

1. Check inclusion / exclusion criteria (on pocked card) to ensure eligibility.
2. Informed consent.
3. Scan QR-code on a *REDOX pocket card* to open REDcap-screening survey on smartphone or tablet (alternative a link on the pocked card can be entered in a PC-browser).
4. Enter screening information as requested and randomize in REDcap.
5. Perform study related procedures.
6. Set-up the O2MATIC and adjust to allocated target.
7. Put O2MATIC on black-screen to ensure blinding.

# Appendix 4: study-related procedures

| Time | **Screening, baseline pre-randomization assessment** | **Randomization** | **12 h post randomization** | **24 h post randomization** | **Discharge** |
| --- | --- | --- | --- | --- | --- |
| Informed consent, patient | x |  |  |  |  |
| Demographics | x |  |  |  |  |
| Inclusion/ exclusion criteria | x |  |  |  |  |
| Medical history | x |  |  |  |  |
| Concomitant medications | x |  |  | x | x |
| Routine blood test | x |  |  | x (morning) |  |
| Arterial blood gas | x |  | x | x |  |
| ECG | x |  |  | x |  |
| Vital signs | x |  | x | x |  |
| Chest x-ray | x |  |  |  |  |
| Echocardiography | x |  |  | x |  |
| Focus lung-ultrasound | X |  |  | x |  |
| ReDS | X |  |  | X |  |
| Patient-dyspnea | X |  |  | X |  |
| Plasma volume | X |  |  | X |  |
| 5Q-DL |  |  |  |  | x |
| Adverse events reporting |  |  |  |  | x |

# Appendix 5: Timeline

[figure not shown]

# Appendix 6: Acronyms and abbreviations

ACC/AHA American College of Cardiology/American Heart Assocation

AE Adverse events

ACE Angiotensin-converting enzyme

ACS Acute Coronary Syndrome

ADHF/AHF Acute decompensated heart failure/Acute heart failure

AF Atrial fibrillation

AKI Acute kidney injury

ARB Angiotensin II receptor blockers

BB Beta-blocker

BMI Body Mass Index

BNP B-type natriuretic peptide

BP Blood pressure

CAD Coronary artery disease

CABG Coronary artery bypass grafting

CHF Chronic heart failure

CI Confidence intervals

CKD Chronic kidney disease

COPD Chronic obstructive pulmonary disease

CRT Cardiac resynchronisation therapy

CXR Chest X-ray

EF Ejection fraction

EGFR Estimated glomerular filtration rate

ELISA Enzyme-linked immunosorbent assay

ESC European Society of Cardiology

FVC Forced vital capacity

HFPEF Heart failure with preserved ejection fraction

HR Hazard ratio

HRQoL Heath-related quality of life

ICD Implantable Cardioverter Defibrillators

ICU Intensive care unit

IHD Ischemic heart disease

INR International normalized ratio

IQR Interquartile range

ITT Intention-to-treat analysis

IV Intravenous

JVP Jugular venous pressure

LVAD Left Ventricular Assist Device

LVEF Left Ventricular Ejection Fraction

MI Myocardial infarction

Minnesota LWHFQ Minnesota Living With Heart Failure Questionnaire

MRA Mineralocorticoid receptor antagonists

NSAIDS Non-steroidal anti-inflammatory drugs

NT-proBNP N-terminus pro B type natriuretic peptide

NYHA New York Heart Association Classification

PCI Percutaneous coronary intervention

PICO Population, intervention, comparison and outcome

QALY Quality-adjusted life years

QOL Quality of life

RAS Renin-angiotensin-system

RCT Random control trial

ROC Receiver operating characteristics

SBP Systolic Blood Pressure

SD Standard deviation

SE Standard error

TIA Transient ischaemic attack

VAS Visual analogue scale
